### Previously collected data

Data abstracted from the DoD medical chart in the GWOT VI study will be used in this study as control variables, or characteristics for stratification based on expert consensus of our clinical team. Table 1 provides a description of the type of information included in the GWOT VI dataset. These DoD data will be merged with national VA health care system data collected as part of the TRACC study (VA inpatient, outpatient, pharmacy and non-VA care [Fee Basis/ Medicare] data). Table 2 provides a description of the variables, definitions and data sources used to create variables. For those who have received VA or Medicare care, we will develop variables related to indicators of persistent morbidity, type of care received, and long-term outcomes. Table 3 provides a specific description of these measures and how they are defined.

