**Table 3 Tab3:** **Indicators of persistent morbidity**

Indicators of persistent morbidity	Data used to identify	Data source
Use of unscheduled or emergency care for vascular issues	DSS Clinic Identifier and ICD-9 Codes	Outpatient (OPC) files; VA-CMS
Use of scheduled care for polytrauma vascular issues	DSS Clinic Identifier and ICD-9 Codes	OPC files; VA-CMS
Long-term use/escalating dose of opioid medications	VA Product, Dose, Day Supply	Pharmacy Benefits Management (PBM) Data; Medicare Part D VA-CMS
	NDC Code	
Trajectory of chronic pain (latent class analysis of pain scores from TRACC)	Pain Score	CDW vitals
Conditions indicative of persistent morbidity (e.g., Venous stasis disease/venous ulcers, lymphedema)	ICD-9 Codes including but not limited to 729.81, 782.3, 729.5, 415.19, 451.11, 451.19 451.83, 451.82, V72.83	PTF, OPC files, VA-CMS
Prescriptions for compression stockings and wound care supplies (e.g., wound vac) indicative of swelling, venous stasis disease	VA Class	PBM Data, VA-CMS Durable Medical Equipment
	XA	
Use of prosthetic/orthotic devices (canes, walkers, special shoes, etc).	Health Care Financing Administration Coding System (HCPCS) Prosthetic and Sensory Aids Service (PSAS) Code;	National Prosthetics database
		CMS Durable Medical Equipment
Additional procedures (open or endovascular) on the injured extremity	CPT-4; ICD-9A procedure codes	OPC/PTF VA-CMS
Chronic antibody use (osteo or other potential infectious issues with the limb)	VA Product	PBM Data; Medicare Part D VA-CMS
Duplex ultrasound, MRA/CTA or angiogram to evaluate the repair	CPT-4 procedure codes including but not limited to 93970, 93971, 93975, 93976, 93978, 93979, 93922, 93923, 93925, 93926, 93930, 93931, 93924	OPC/PTF; VA-CMS
Mean pain scores over 4	Pain Score Mean per year	Corporate data warehouse Vital Signs
Proportion of VA care	Visits VA/ Total Visits	OPC/PTF; VA CMS outpatient/inpatient
Mortality	Date of Death	VA Vital Status file

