### Analytic plan

To address the first aim, we will compare injury, demographic and geospatial characteristics of patients IILS and identify late vascular surgery related limb complications and health care utilization in Veterans receiving VA vs. non-VA care using merged VA + VA-Medicare and DoD study data. We will identify vascular procedures performed, limb salvage survival time, and indicators of persistent morbidity over time (*e.g*., frequent/emergency care for vascular-related conditions, venous stasis disease, prosthetic use, long-term opioid therapy [VA patients only]). We will calculate descriptive statistics for all IILS patients’ demographic characteristics, long-term clinical outcomes (surgery related limb complications, time to amputation, persistent morbidity), and healthcare utilization (note that long-term use of opioid therapy will be assessed only among VA patients). We will also compare these descriptive statistics between those who received VA vs. non-VA care using chi-square tests for categorical variables and t-tests for continuous variables (with appropriate Box-Cox power transformation if necessary).

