We will also conduct generalizability analysis using the inverse propensity probability weight technique. [53, 54] The goal is to examine whether the outcome model derived from the VA IILS patients (as described above) can be generalized to the non-VA IILS patients. We first derive model estimates for the VA cohort, then compute the propensity score for receiving non-VA care by modeling the log-odds of receiving non-VA care (vs. VA care) as a linear function of baseline covariates. The inverse propensity weighting is used to calibrate the outcome model derived from the VA IILS patients to the non-VA IILS patients. Finally we assess model generalizability by comparing model estimates between the VA vs. non-VA patients using the diagnostic method by Stuart et al. [55] This generalizability method does not require collecting outcomes for non-VA patients. However the credibility of this method relies on the “ignorability” assumption to hold true: conditioning on the covariates, the counterfactual outcomes of the non-VA patients (the patency outcomes should they receive VA care) would have been the same as the outcomes of the VA patients, and similarly, the counterfactual outcomes of the VA patients (the patency outcomes should they receive non-VA care) would have been the same as the outcomes of the non-VA patients.

Based on preliminary data from the TRACC study, we anticipate that the proportion of OEF/OIF/OND VA patients with ILLS will receive antiplatelet agents/statins/or yearly duplex ultrasound will be no greater than 44.7%. We also assume that the mean vascular repair patency falls between 50%-60%, and that the increased patency due to receiving antiplatelet agents/statins/or yearly duplex ultrasound is no less than 12% (conservatively). Under these conditions, the study will have ≥0.84 power to determine if Vascular Preventive Care processes are associated with positive patient outcomes.

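### Aim 1 tests VA against non-VA Veterans on outcomes whose post-separation ascertainment differs by group

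*Protocol article*

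**What the plan says.** The Analytic plan for Aim 1 names "long-term clinical outcomes (surgery related limb complications, time to amputation, persistent morbidity), and healthcare utilization" among the descriptive statistics for all limb-salvage patients. It continues: "We will also compare these descriptive statistics between those who received VA vs. non-VA care", by chi-square test or t-test according to the type of variable. The Abstract puts this comparison first among the primary outcome measures.

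The sources for these outcomes are set out elsewhere in the article:

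- Previously collected data: the non-VA care data merged into the file are Fee Basis and Medicare. The section adds: "For those who have received VA or Medicare care, we will develop variables related to indicators of persistent morbidity", together with type of care and long-term outcomes.
- Table 3: every source named for the 13 indicators of persistent morbidity is a VA or CMS file. The yearly mean pain score comes from "Corporate data warehouse Vital Signs", and the pain trajectory comes from the same warehouse.
- Study sample and VA medical chart abstraction: the database and chart components cover those who received VA care, about 700 people.

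Only one outcome is restricted to VA patients: "note that long-term use of opioid therapy will be assessed only among VA patients". For Veterans without VA care, the Study sample section says only that further analyses depend on what data are available.

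**The concern.** A VA user's later complications can be read from VA encounter files, pharmacy, prosthetics, vital signs and abstracted charts, as well as from Fee Basis and Medicare. A non-VA Veteran's later complications can be read only where Fee Basis or Medicare holds a record. Care paid for in any other way leaves no trace after separation. The Background describes the trauma population as mostly younger, so wide Medicare enrolment cannot be presumed.

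The grouping variable thus governs ascertainment of the outcome, and a chi-square or t-test cannot separate a difference in events from a difference in visibility. The study is meant to inform care planning and the transition from DoD to VA, so an apparent excess of complications or utilisation in VA users could be taken as a finding about VA care when it reflects data coverage.

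**Working it through.** **1. Which outcomes are recorded alike?** Setting the data sections side by side:

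| Variable | Source named | Same ascertainment in both groups? |
|---|---|---|
| Injury, repair, in-service complications, follow-up and amputation status | DoD chart abstraction (Table 1) | Yes |
| Age, sex, race/ethnicity, education, rank, component, branch | Roster file (Table 2) | Yes |
| Post-separation care, procedures and diagnoses | VA files and VA-CMS (Table 3) | No |
| Pain trajectory; mean pain score | VA vital signs only | No; non-users have no value |
| Long-term opioid use | VA pharmacy and Medicare Part D, but restricted to VA patients in the text | Not compared |
| Proportion of VA care | VA visits / total visits | Nearly restates the grouping |
| Mortality | VA Vital Status file | Not stated whether it covers non-users |

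Three of the 13 Table 3 indicators (pain trajectory, mean pain score, mortality) list only a VA file. The text restricts a fourth, opioid use, to VA patients.

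**2. The plan's own figure.** The article gives no power, alpha or effect size for this comparison. The only relevant figure is the VA group of about 700. From the stated inputs, 1,266 × 0.59 = 747, so 700 is somewhat lower than the arithmetic gives. This does not affect the point. The non-VA remainder is 1,266 − 700 = 566 (or 1,266 − 747 = 519).

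**3. Illustration, if unseen Veterans count as event-free.** Let the true rate be p in both groups and let c be the share of non-VA events that the linked files capture. The observed rates are then p₁ = p and p₂ = c × p. With two-sided alpha 0.05 (assumed),

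P(significant) = Φ[(|p₁ − p₂| − 1.96 × SE₀) / SE₁],

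where SE₀ uses the pooled proportion and SE₁ the two separate ones. The documents give no c, so a range is shown. The rate p = 15% is the late-amputation figure that the Background cites for lower-extremity injuries.

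For p = 0.15, c = 0.7: p₂ = 0.105; pooled proportion = (700 × 0.15 + 566 × 0.105) / 1,266 = 0.130; SE₀ = 0.0190; SE₁ = 0.0187; P = Φ[(0.045 − 1.96 × 0.0190) / 0.0187] = 0.66.

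Chance of a false significant difference, 700 against 566:

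| True rate | c = 0.9 | c = 0.8 | c = 0.7 | c = 0.5 |
|---|---|---|---|---|
| 10% | 0.086 | 0.230 | 0.470 | 0.919 |
| 15% | 0.113 | 0.338 | 0.661 | 0.988 |
| 30% | 0.215 | 0.665 | 0.955 | >0.999 |
| 50% | 0.425 | 0.946 | >0.999 | >0.999 |

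With 747 against 519 and a 15% rate, the values are 0.111, 0.328, 0.648 and 0.987.

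**4. If unseen Veterans count as missing.** The table above then does not apply. The non-VA group becomes those with a Medicare or Fee Basis record, who are selected on enrolment or on having sought such care. The documents give nothing from which to derive the direction or size of that bias.

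**The case against.** The first aim is described as descriptive, the contrasts are unadjusted, and no power is claimed for them. A condensed article may leave coding rules to a fuller document. Nowhere does it say that an untraced Veteran is scored as event-free. The sentence that builds outcome variables for those with VA or Medicare care points rather to missing values, and non-users plainly have no pain score. All of this stands, but it does not rescue the comparison. The article itself fixes the groups, outcomes, sources and tests, and neither coding makes them fit together. The general remark about data limits sets no rule on who is observable.

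Three stronger readings are tempting and are not supported:

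- A reader might infer that the plan will necessarily show far more complications in VA users. That depends on the coding and on the capture share, neither of which is given. At a 15% rate and 90% capture, the chance of a false difference is only 11%.
- A reader might infer that non-VA Veterans' events can be seen only in claims. Table 1 shows that DoD charts record complications, follow-up care and amputation status whatever the later use of VA. The Background puts late amputations at 12 weeks to 5.5 years after injury, so some may precede separation. The gap concerns post-separation events and the Table 3 indicators.
- A reader might infer that the generalizability analysis contradicts itself, since it says "This generalizability method does not require collecting outcomes for non-VA patients" and also "Finally we assess model generalizability by comparing model estimates between the VA vs. non-VA patients". The text just before calibrates the VA outcome model to the non-VA patients by weighting. The natural reading is VA estimates set against VA estimates reweighted to the non-VA covariate mix, which needs no non-VA outcomes.

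**Conclusion.** The point holds for post-separation complications, amputation, persistent morbidity, pain and utilisation. It does not touch the injury and demographic comparisons drawn from DoD charts and the roster file. Ascertainment differs by group under either way of handling Veterans without a record: one biases the result towards more events in VA users, and the other leaves a selected comparison group. Restricting opioid therapy to VA patients deals with one variable and leaves both pain indicators, which also come only from VA records, in the comparison.

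The size is conditional. Under the event-free coding, with equal true rates of 15%, 700 against 566 and alpha 0.05, a false significant difference occurs about 11%, 66% or 99% of the time at 90%, 70% or 50% capture. Capture share, alpha and the use of 15% as the event rate are assumptions for illustration, not predictions. Because the comparison stands first among the primary outcome measures, it should be corrected before Aim 1 is analysed.

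**What to change.** In the Aim 1 analysis text:

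- Limit the VA against non-VA tests to variables recorded alike in both groups: DoD injury, repair and in-service follow-up data; roster demographics; location; and mortality only if the Vital Status file is confirmed to cover non-users. For location, confirm a source common to both groups, since Table 2 appears to list residence under the VA care files.
- Report post-separation complications, amputation, morbidity, pain and utilisation for VA users only. Alternatively, contrast the outcomes that Medicare records in Medicare-enrolled person-time in both groups, labelled as that subgroup. Pain scores stay VA-only either way.
- State how a Veteran with no record is handled, keeping no event distinct from not observed.
- Do not compare the proportion of VA care as a morbidity indicator.

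This needs new wording and no new data collection, apart from confirming the coverage of the mortality and location sources. The cost is a narrower outcome comparison between VA and non-VA Veterans, confined to what the sources can support.

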## Background

### Combat-related vascular injuries

Wartime injuries have been studied during every major conflict of the 20^th^ and 21^st^ centuries. Hughes in Korea [1], and Rich in Vietnam [2], each advanced the care of Service members with vascular injuries. Ligation of injured blood vessels and the resultant high limb loss rate in World War II gave way to arterial and venous repair in the Korean and Vietnam Wars. With these advances, life and limb salvage rates improved dramatically in the short and mid-term time frame. However, long term outcomes following the definitive repair of wartime vascular injuries by a vascular specialist in the theater of war have not previously been evaluated. *To improve care, we must provide long term follow up and define the natural history of wartime vascular injury over an injured Soldier’s lifetime.*

Improvements in battlefield protection devices, casualty evacuation and medical care have enhanced survival rates, currently over 90%, following combat injuries. Many survivors of once-lethal injuries now require prolonged medical and rehabilitation care for polytrauma injuries [3]. Rapid aero-medical evacuation from the battlefield to definitive surgical care has been a major contributor to improved initial limb salvage rates, allowing access to vascular surgery care more rapidly, thereby decreasing ischemia times of injured limbs. The in-theatre use of diagnostic angiography and endovascular treatments has enabled more attempts at limb salvage after extremity vascular injury [4]. Additionally, patients usually leave the theater of war within 24 hours after receiving initial medical treatment [4–6]. Subsequent care is obtained in several locations while en route to the United States, and in military trauma centers in the U.S. Once the acute hospitalization phase is completed, and longer term rehabilitation at Walter Reed National Military Medical Center or the San Antonio Military Medical Center is completed, the patient will be released to the home station and the associated military treatment facility (MTF) or to the local community. In the event that the Service member separates from the DoD, care is often transferred to the Veterans Administration (VA), especially when high service-connected ratings of disability are present. Most of the MTFs do not have a vascular surgeon or non-invasive vascular laboratory (duplex ultrasound) to provide long-term surveillance of the vascular repair.

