**Figure 1 Fig1:**
[figure not shown]
**Donabedian’s model of quality of care posits that processes of care (Vascular Preventive Care) may be associated with patient outcomes.** However, the complex relationships among demographic characteristics, initial injury severity, and comorbid physical and psychiatric conditions require careful attention to the potential for confounding and effect modifiers. While it is also important to control for demographic characteristics, particular concern is focused on controlling for disease burden and initial injury characteristics since these may have substantial impact on the outcome that is unrelated to the initial vascular injury and preventive care.

Because little is known about the natural history of these types of injuries given modern combat casualty care, our first aim is to describe the population of interest including initial and subsequent treatment in the DoD. Our second aim is to describe extant preventive care processes provided for individuals with IILS by the VA since best practices for individuals with traumatic vascular repair have not been established and little is known about the types of preventive care available. Because research in other types of care have found that processes of care identified as best practices are associated with patient outcomes [35], our third aim is to identify the association of Vascular Preventive Care with patient outcomes [36] such as measures of persistent morbidity, adjusting for potential confounders, and effect modifiers. While it is also important to control for demographic characteristics, particular concern will be focused on controlling for traumatic brain injury, physical and psychiatric disease burden, and initial injury characteristics since these may have substantial impact on the outcome that is unrelated to the initial vascular injury and preventive care [37]. If Vascular Preventive Care processes are associated with positive patient outcomes, there will be support for these care processes as best practices [38].

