**Table 1 Tab1:** **Information obtained from DoD chart abstraction: baseline polytrauma injury characteristics**

Type of variable	Information
Demographics	Age, sex, race/ethnicity and service branch
Initial Injury Information	Date, primary cause/mechanism
Vascular Extremity Details	Arterial/venous injury location, pre/post repair details, and complications.
Ortho/Nerve Extremity Details	Associated soft tissue/bone/nerve injuries, methods of repair, flap status.
Follow Up Care	Dates, location, and CT/MRI/Angio/Duplex studies.
Functional/ Amputation status	Limitations, context of amputation if relevant

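### The first aim tests VA versus non-VA outcomes without adjustment for injury characteristics, so the crude contrast may reflect case mix rather than care system

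*Protocol article*

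**What the plan says.** In the Analytic plan, the first aim produces descriptive statistics for demographic characteristics and for "long-term clinical outcomes (surgery related limb complications, time to amputation, persistent morbidity), and healthcare utilization". The plan will then "compare these descriptive statistics between those who received VA vs. non-VA care using chi-square tests for categorical variables and t-tests for continuous variables", with a power transformation for continuous variables if needed. No adjustment is attached to this step.

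Elsewhere the article says:

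- **Background, Combat-related vascular injuries:** after separation from the DoD, "care is often transferred to the Veterans Administration (VA), especially when high service-connected ratings of disability are present".
- **Figure 1 legend:** "particular concern is focused on controlling for disease burden and initial injury characteristics", because these may affect outcome independently of the vascular injury and preventive care.
- **Previously collected data:** the DoD chart data "will be used in this study as control variables, or characteristics for stratification based on expert consensus of our clinical team".
- **Table 1:** the data held include demographics, date and mechanism of injury, location of the arterial or venous injury, repair details, and, under orthopaedic and nerve details, "Associated soft tissue/bone/nerve injuries, methods of repair, flap status".
- **Analytic plan, generalizability analysis:** the plan will "compute the propensity score for receiving non-VA care" from baseline covariates, in order to carry the VA outcome model over to non-VA patients.

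**The concern.** A crude comparison of baseline characteristics between care systems is what a descriptive aim calls for. A crude significance test on outcomes is different. If Veterans with more complex injuries are more likely to use the VA, complications, morbidity and utilization will differ between the groups even when care is equally good. A VA excess could then be read as a care problem, or a real benefit of VA care could be hidden.

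The article names this type of confounder and holds the data to address it, but does not use them in this one comparison. The contrast is also prominent. The Aims section makes late limb complications in VA versus non-VA Veterans part of the study goal, and the Discussion expects the results to inform resource planning and DoD-to-VA transitions.

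**Working it through.** **Where adjustment is specified.** Setting the parts of the Analytic plan side by side:

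| Analysis | Adjustment named |
|---|---|
| First aim, VA vs non-VA outcomes | None |
| Second aim, preventive care and patency | Covariates, facility random effect, inverse propensity weights |
| Generalizability to non-VA patients | Propensity score for receiving non-VA care |
| Patient-reported outcomes | Covariates, plus injury-severity strata as a secondary analysis |

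Only the first row has none.

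**Size.** The plan gives no power, effect size or case mix for the first aim, so there is no stated figure to reproduce. The following is an illustration.

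Inputs from the document (Study sample): about 1,266 separated Veterans and about 700 expected in VA care, which leaves 1,266 − 700 = 566.

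Assumed inputs: the share of complex injuries in each group, the late-complication risk by complexity (the same in both care systems, so there is no true care effect), and a two-sided 5% level.

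Crude rate = share complex × risk complex + (1 − share complex) × risk simple.

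Central case, with shares 50% (VA) and 30% (non-VA) and risks 25% and 8%:
- VA: 0.50 × 0.25 + 0.50 × 0.08 = 16.5%
- Non-VA: 0.30 × 0.25 + 0.70 × 0.08 = 13.1%
- False difference: 3.4 points
- Pooled rate: (700 × 0.165 + 566 × 0.131) / 1,266 = 0.150
- Standard error under the null: √[0.150 × 0.850 × (1/700 + 1/566)] = 0.0202; unpooled: 0.0200
- Rejection probability: Φ[(0.034 − 1.96 × 0.0202) / 0.0200] ≈ 0.39

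The same formula at the two ends of the assumed range:

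| Shares complex (VA, non-VA) | Risks (complex, simple) | Crude rates | Difference | Rejection |
|---|---|---|---|---|
| 45%, 35% | 22%, 10% | 15.4%, 14.2% | 1.2 points | 9% |
| 50%, 30% | 25%, 8% | 16.5%, 13.1% | 3.4 points | 39% |
| 60%, 30% | 25%, 8% | 18.2%, 13.1% | 5.1 points | 70% |

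**If fewer non-VA outcomes are available.** With 700 VA patients and the central rates, rejection falls from 39% at 566 non-VA patients to 27% at 300, 20% at 200 and 12% at 100. The low case falls from 9% to about 5.5% at 100. The false difference itself does not shrink, provided the patients with data have the same case mix.

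**Does adjustment remove it?** In simulation (4,000 datasets per scenario, 700 vs 566, 10% risk in less severe injuries, 20% to 40% in severe ones, severe shares of 45% vs 35%, 50% vs 30% and 60% vs 30%), the crude chi-square rejected in about 8% to 96% of datasets. A Mantel-Haenszel test stratified by severity rejected in 4.4% to 5.5%. With equal case mix (40% in both groups) the crude test stayed near 5%. This shows that stratification works when severity is measured; it says nothing about unmeasured severity.

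**The case against.** The strongest defence is that the first aim is descriptive. The Aims section says so, and nowhere does the plan commit to attributing a first-aim difference to the care system. In the Abstract, the verb for characteristics is to compare, and for complications and utilization only to identify. Injury characteristics will be reported by group, so imbalance would be visible. Unadjusted burden and utilization are also what a planner of services needs. All of this stands, and it is why the crude figures should be kept. It does not settle the matter, because the Analytic plan attaches significance tests between care systems to outcomes.

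A second defence is that the statement on previously collected data covers the whole study, and that a condensed article may leave covariate lists to a fuller plan. The statement is general, however, and tied to no aim. Where the article comes to the method for this comparison, it names one, without adjustment.

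A third objection also stands: disability ratings are assigned after injury and are not specific to the limb. A reader might infer from the Background that VA patients had worse limb injuries at baseline. The document does not say this; the rating is only a proxy for injury severity.

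Finally, the 566 is an upper figure. The Study sample section limits analyses of those without VA care to the data available.

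**Conclusion.** The point holds as a weakness in a stated method. The first-aim outcome tests are unadjusted, while the article itself says injury characteristics need control and holds them for that use. The crude contrast may therefore reflect case mix.

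The size is unknown. The range of about 9% to 70% false rejection rests on assumed complex-injury shares and risks, on no true care effect, and on outcomes being available for all 566 non-VA Veterans.

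Two stronger readings are not supported. One is that a significant VA excess is to be expected: no case mix by care system is given, and even the central illustration rejects in fewer than half of studies. The other is that the crude comparison is wrong in itself and should be replaced: it remains valid for describing actual burden and use.

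**What to change.** 1. Keep the chi-square and t-tests for injury, demographic and geospatial characteristics and for describing actual burden and utilization, and label the outcome results as unadjusted.
2. Add a VA versus non-VA comparison of limb complications, persistent morbidity and utilization that is adjusted for, stratified by or propensity-weighted on the Table 1 baseline variables: mechanism, vessel location, associated bone, nerve and soft-tissue injury, repair details, injury date, age and service branch. The propensity model for non-VA care could be extended to this use. It is planned for the generalizability analysis and does not yet exist.
3. State that any conclusion about a difference between care systems rests on the adjusted comparison, and report the number of non-VA Veterans with outcome data.

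The cost is plan wording and some programming, with no new data collection. Intervals may be wider if the two groups overlap poorly, and residual confounding by unmeasured severity will remain and should be acknowledged.

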**Eligibility flow diagram showing DoD chart abstractions using the Department of Defense Trauma Registry (DoDTR).**

### Study procedures

The VAVIS protocol was reviewed and approved by the VA Central IRB. This three component study will begin first by compiling data previously collected from DoD and VA (FY01-FY14), linking files from each source using the unique identifier. Once VA patients in the confirmed IILS cohort are identified, we will conduct medical chart abstraction of VA electronic medical records, and conduct a patient interview and survey to obtain patient reported outcomes. The study will start on April 1, 2015 and will be open for three years.

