### VA medical chart abstraction

We will access the electronic medical record for any VA patient with IILS from the time of VA entry to the time of abstraction, with special attention to functional outcomes including physical therapy, prosthetic care, and care for vascular injuries or conditions such as skin ulcers that may result from graft failure or complications of the initial injury. After development of the electronic data collection template, database, and training, the PI and the chart abstractors will independently review 10 charts and meet together to identify inconsistencies, errors, or disagreements and resolve any by consensus. This will continue until there is 90% agreement on all items abstracted.

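### The comparison of health care utilization between VA and non-VA Veterans makes no stated allowance for unequal observation time

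*Protocol article*

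**What the plan says.** The abstract lists utilization in VA versus non-VA care under the primary outcome measures. The Analytic plan repeats this for the first aim: "health care utilization in Veterans receiving VA vs. non-VA care". It then lists the quantities to be described, including "healthcare utilization (note that long-term use of opioid therapy will be assessed only among VA patients", and says that these are also compared between the two care groups. Categorical variables go to chi-square tests. Continuous variables go to "t-tests for continuous variables (with appropriate Box-Cox power transformation if necessary". No other method is named for this comparison.

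Observation time is specific to the person. The database component begins by "compiling data previously collected from DoD and VA (FY01-FY14". Chart review runs "from the time of VA entry to the time of abstraction". Table 2 carries each person's military discharge date and Table 3 the date of death.

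The scale of utilization is left open. Table 3 has items such as "Use of unscheduled or emergency care for vascular issues", which could be a count, a rate or yes/no. The one visit measure with a formula is a share of care, "Visits VA/ Total Visits". Pain is annualised ("Pain Score Mean per year"); visits and procedures are not.

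**The concern.** Visits, emergency attendances and repeat procedures accumulate with time. A Veteran observed for eight years will have more of them than one observed for three, even if both use care at the same rate. The VA group consists of those who have received VA care, and Veterans separated for longer have had more time to enter it. A difference in mean observation time between the groups is therefore plausible, though the article reports none.

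If the named tests are applied to accumulated totals, a difference in time since separation would be read as a difference in use of care. Turning totals into yes/no does not avoid this, because the chance of any use also rises with time. The Discussion says the results are meant to guide planning, resource use and transitions between the two care systems, so a spurious difference would matter.

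A smaller point concerns the transformation. Plain Box-Cox requires strictly positive values, so it is undefined for a Veteran with no visits, and no shift is given.

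**Working it through.** The article states no visit rate, follow-up time, significance level or power for the first aim, so there is no figure to reproduce. The check asks how often the named tests reject when the true yearly rates are equal.

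**Inputs from Study sample.** About 700 VA patients and about 1,266 separated from service, so 1,266 − 700 = 566 non-VA. (The 59% given there yields 1,266 × 0.59 = 747; the article's rounder 700 is used.)

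**Assumptions not in the article.** Two-sided 5% level. Rate λ of 0.2 or 1.0 visits a year, the same in both groups. Gamma-Poisson counts with overdispersion 1.5. Each person's follow-up uniform between 0.5 and 1.5 times the group mean m. VA mean 5 years; non-VA mean 5, 4.5 or 4 years.

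**By formula.** For uniform follow-up, Var(T) = m²/12 and E(T²) = 13m²/12. The variance of a person's total is

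V(m) = λm + λ²m²(1.5 × 13/12 + 1/12) = λm + 1.708 λ²m².

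The expected difference in totals is λ(m₁ − m₂), with standard error √(V(m₁)/700 + V(m₂)/566).

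- λ = 1.0, 5 vs 4.5 years: V = 47.71 and 39.09; SE = 0.370; z = 0.5/0.370 = 1.35; rejection 27%.
- λ = 1.0, 5 vs 4 years: V = 47.71 and 31.33; SE = 0.351; z = 1.0/0.351 = 2.85; rejection 81%.
- λ = 0.2, 5 vs 4.5 years: V = 2.71 and 2.28; SE = 0.0889; z = 0.1/0.0889 = 1.12; rejection 20%.
- λ = 0.2, 5 vs 4 years: V = 2.71 and 1.89; SE = 0.0849; z = 0.2/0.0849 = 2.36; rejection 65%.

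**By simulation.** There were 1,000 runs per setting with Welch t-tests, and 2,000 runs for the chi-square row. Entries are rejection under equal rates at λ = 0.2 / λ = 1.0.

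| Analysis | 5 vs 5 years | 5 vs 4.5 | 5 vs 4 |
|---|---|---|---|
| t-test on totals | 6.0% / 6.5% | 23% / 29% | 68% / 82% |
| t-test on Box-Cox(count + 1) | 5.5% / 6.4% | 17% / 22% | 53% / 71% |
| Chi-square on any use | 5% / 5% | 13% / 9% | 38% / 28% |
| t-test on visits per person-year | 5.6% / 5.9% | 5.3% / 5.4% | 5.5% / 4.2% |
| Robust rate ratio using person-time | 5.9% / 6.3% | 6.0% / 5.4% | 6.6% / 4.6% |

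The formula and the simulation agree within a few percentage points. Simulation error is at most √(0.25/1,000) = 1.6 points (one standard error). The shift used for Box-Cox was chosen for the check, because the article gives none.

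**Zeros.** In these settings 25-57% of persons had no visits. With equal mean follow-up the t-test stayed near its level even at 55% zeros. The inflation comes from the follow-up gap, not from the zeros.

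**The case against.** The strongest reply is that the article never says raw totals are compared. It assigns tests by type of variable and does not say which type utilization is. Visits per year, any use and share of visits all fit its wording, and a condensed article may leave that derivation to a fuller plan. A t-test on visits per person-year follows the quoted sentence as written and keeps its level. This stands: a reader might infer that the plan commits to raw counts, or that a t-test by its nature ignores person-time, and the text supports neither reading.

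The yes/no reading does not rescue the rule, however, because ever-use also accumulates with time. The share-of-care formula measures where care was received, not how much. Only a per-time scale escapes, and the article gives one to pain and none to visits or procedures.

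A second reply is that Box-Cox is optional. That also stands. A reader might infer that the named method cannot cope with Veterans who have no visits. But the untransformed t-test accepts zeros, a shifted Box-Cox runs, and zeros alone did no harm in the check. What remains is that the shift is unspecified.

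A third reply is that the size rests on a follow-up gap that the article does not report. That is correct: with equal means there is no material inflation.

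Finally, a rate model is not a full cure. Non-VA care is seen only through the Fee Basis and Medicare files, and Study sample limits non-VA analyses to the data available.

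**Conclusion.** The point holds in a limited form. A comparison listed under the primary outcome measures has a stated test rule with no allowance for observation time, while the article's own data sources make that time vary between persons. Compared as totals or as ever-use, equal rates can test as different.

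Under the assumptions above, a half-year gap in mean follow-up raises the false-positive rate from about 6% to 23-29% for totals and to 9-13% for ever-use. A one-year gap raises it to 68-82% and 28-38%. Person-time methods stay at 4-7%. Rates, dispersion and gap are all assumed, so these figures show sensitivity and do not estimate the error in this study. The plan should be changed, because the remedy is cheap and the comparison is prominent, but it has not been shown to produce a false result.

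**What to change.** For visit and procedure counts, replace the t-test/Box-Cox rule with a negative-binomial or robust Poisson model with a log person-years offset, and report rate ratios with 95% confidence intervals. At minimum, define these outcomes as visits or procedures per person-year before any t-test. Report the proportion with any use by a method that also allows for observation time. Keep t-tests for truly continuous characteristics such as age.

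Define person-time as the period during which a person's care can be seen in the linked VA, Fee Basis or Medicare files, ending at death or data cut-off. Do not run it from discharge for everyone: that would count years of unobserved private care as years without visits. State that care outside those files is not captured.

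The cost is mainly wording in the analysis plan. Discharge dates (Table 2) and dates of death (Table 3) are already held. The one extra task is a rule for when each person's care is observable, which the tables do not now define.
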